### Withdrawal and termination

2.11

Participants may voluntarily withdraw from the study for any reason at any time. Participants will be considered withdrawn if they state an intention to withdraw, reach composite renal endpoint events, or become lost to follow-up for any other reason. When withdrawal occurs, the researcher must determine the primary reason for premature withdrawal from the study and record this information on the Case Report Form (CRF). The research team and study doctor may remove a participant from further participation in this study if (1) staying in the study would be unsafe or harmful to the participant; (2) the participant needs treatment that is not allowed in this study; (3) participant fails to follow instructions; (4) participant becomes pregnant. This study may be stopped for several reasons, including unacceptable side effects, the intervention being shown to have no effect, or being effective with no need for further investigation.

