#### Intervention

2.8.3

TQF or placebo medications will be given to the participants by a registered pharmacist according to the randomized numbers. TQF or TQF placebo granules of 15 grams will be taken orally twice daily by dissolving in boiled water. The participants will take the granules for 48 weeks. A 30-day Medication Diary will be delivered to the participants every 4 weeks. The packets of taken granules and left-over medications will be collected and recorded in the Compliance Check Form. Participants allocated to the placebo group can take the TQF granule for 12 weeks at no cost after the follow-up period. A valid and reproducible Dampness Syndrome Scale of Chinese Medicine, which strictly follows the international standard for scale development, will be used to measure the changes in dampness syndrome (35).

Chinese herbal formulas or Chinese patent medicine that have the function of tonifying the Kidney and dispelling dampness are prohibited in this trial to avoid contamination of the intervention. Those formulas and patent medicine include but are not limited to *Huangkui* Capsule, *Yishen Huazhuo* Granule, *Yishen Huashi* Granule, *Niao Du Qing* Granule, and *Niao Du Kang* Granule. The participant who has taken these drugs for more than one week will be withdrawn from this study.

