#### Feasibility

2.9.1

The feasibility of TQF and trial design will be explored as the primary outcome. The key domains for the assessment include recruitment, intervention protocol, outcome assessments, and data collection methods. The eligibility, recruitment, retention, and completion rates will be investigated at the end of the pilot trial:

1) Eligibility rate: the percentage of eligible participants over the number of screened participants;2) Recruitment rate: the percentage of recruited participants over eligible participants;3) Retention rate: the percentages of participants in both groups at the end of treatment and end of follow-up over the number of participants randomized;4) Completion rate: the percentage of participants who completed the treatment phase over the number of participants randomized.

Semi-structured interviews will be conducted to further explore the feasibility among the trial participants.

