#### Efficacy outcomes

2.9.2

The efficacy of TQF for people with stage 2-4 DKD will be assessed on renal-related outcomes every 12 weeks.

The eGFR slope will be measured at the end of the treatment. eGFR slope is a validated surrogate endpoint for clinical trials to indicate kidney disease progression (33, 34). The Chronic Kidney Disease Epidemiology Collaboration (CKD-EPI) equation will be used to calculate eGFR (36).

Other efficacy outcomes will be measured from baseline to the end of treatment: changes in UACR, UPCR, serum creatinine, blood urea nitrogen, uric acid, HbA1c, fasting blood glucose (FBG), and blood lipids (cholesterol, triglycerides, low-density lipoprotein cholesterol, and high-density lipoprotein cholesterol). The laboratory equipment for all the laboratory outcomes will be standardized and follow a consistent operating procedure. Additionally, the changes in the score of the Dampness Syndrome Scale of Chinese medicine and the survival time of renal composite endpoint events will also be evaluated (35). The survival time is defined as starting from baseline to the occurrence of any of the below composite endpoints (37): receipt of a kidney transplant, initiation of maintenance dialysis, death from kidney failure, a sustained low eGFR, and a sustained percent decline in eGFR.

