### Statistical analysis

2.14

The quantitative data will be processed and analyzed by an independent statistician at GPHCM using PASW 18.0 (IBM SPSS Inc., Armonk, New York, USA) and Stata (Version 15.0, Stata Corp. College Station, TX, USA) with two-tailed 5% significance.

We will perform the primary analysis on the full analysis population following the Intent-to-Treat (ITT) principle. The full analysis population refers to randomized participants who received at least one dose of treatment and had baseline data along with at least one post-baseline efficacy assessment. We will also conduct a per-protocol analysis as a secondary analysis, including participants who completed the study without significant protocol violations. Safety analysis will be performed on the randomized participants who have received at least one dose of TQF or placebo.

Descriptive analysis will be performed on demographic and baseline characteristics. Categorical variables will be summarized as frequencies and percentages. The difference between the two groups will be assessed with a *chi*-squared test. Continuous variables will be reported as means with standard deviations for or medians with interquartile ranges. The difference between the two groups will be detected by Student’s *t*-test for normally distributed data, or the Mann-Whitney U-test for non-normally distributed variables.

The primary efficacy outcome eGFR slope will be assessed through a linear mixed-effects model in which treatment and the interaction of treatment and time are treated as a fixed effect while the time effect is a random effect using an unstructured covariance matrix. A secondary analysis for the eGFR slope will be conducted through the superiority test with a 95% confidence interval (CI), to explore any clinical disparities associated with TQF.

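### Renal endpoints and prohibited herb use are treated as withdrawal from the study, with no provision for later visits: a poor fit with the ITT principle, and endpoint cases count as not retained

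*Protocol article*

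**What the plan says.** **Withdrawal (Protocol article, 2.11).** "Participants will be considered withdrawn if they state an intention to withdraw, reach composite renal endpoint events"; the sentence goes on to loss to follow-up. For every such case "the researcher must determine the primary reason for premature withdrawal from the study" and record it on the CRF. A participant may also be removed at the team's discretion, for example where "3) participant fails to follow instructions".

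**Prohibited herbs (2.8.3).** "The participant who has taken these drugs for more than one week will be withdrawn from this study".

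**What the composite contains (2.9.2).** Besides transplant, maintenance dialysis and death from kidney failure, it includes "a sustained low eGFR, and a sustained percent decline in eGFR". No thresholds are printed.

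**Analysis (2.14).** "We will perform the primary analysis on the full analysis population following the Intent-to-Treat (ITT) principle". That population is everyone randomized and dosed who "had baseline data along with at least one post-baseline efficacy assessment". The eGFR slope is the primary efficacy outcome and is analysed by a linear mixed-effects model. Missing values are replaced by linear trend at point, with LOCF as fallback, and a sensitivity analysis omits imputation.

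**Feasibility, the primary outcome (2.9.1).** "Retention rate: the percentages of participants in both groups at the end of treatment and end of follow-up over the number of participants randomized". The completion rate uses the same denominator. Neither rate makes an exception for endpoint events.

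**The concern.** The article has one category, withdrawn, for three different things: a participant who leaves, a participant whose kidney function has reached an endpoint, and a participant who has used a prohibited product. It does not distinguish stopping the granules from leaving the study.

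Three consequences follow if the text is applied as written.

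- Collection of eGFR stops because of the course of eGFR, the variable whose slope is the main efficacy measure. The remaining values are then imputed.
- Withdrawal for prohibited herbs or non-adherence stops observation because of behaviour after randomization. Following everyone regardless of such events is the substance of the ITT principle that section 2.14 invokes.
- A participant who supplies an efficacy event is scored as a retention failure. Retention and completion are part of the primary outcome and are meant to inform a full-scale trial, so they should measure whether participants can be kept, not how often the disease progresses.

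**Working it through.** **1. The plan's own attrition figure.** Section 2.5 gives 25 per arm and about 15% attrition. 25 / (1 − 0.15) = 29.4, rounded up to 30 per arm, 60 in total. This reproduces. Allowed loss: 0.15 × 60 = 9, so expected retention is 51/60 = 85.0%.

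**2. Cost per case.** 1/60 = 1.7 points. If the 9 losses are all ordinary attrition and endpoint withdrawals come on top:

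| Endpoint withdrawals | Retention |
|---|---|
| 0 | 51/60 = 85.0% |
| 2 | 49/60 = 81.7% |
| 3 | 48/60 = 80.0% |
| 4 | 47/60 = 78.3% |

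**3. How many cases.** The article gives no thresholds or variances, so this step is a simulation under assumptions.

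- From the documents: eligible eGFR 15 to below 90 (2.4.1); control decline 3.79, taken as yearly, and a difference of 0.75 (2.5); visits every 12 weeks (Table 1).
- Assumed: baseline eGFR uniform over 15 to 90; between-person slope SD 3 to 5; residual SD 4; endpoint = eGFR below 15, or a fall of 30% or 40% from baseline, at two consecutive visits.
- Model: y = b + s·t + e, with t = 0, 12, 24, 36, 48 weeks from randomization; mean s = −3.79 (control) and −3.79 + 0.75 = −3.04 (TQF); measured baseline at least 15; 400,000 simulated participants per arm; withdrawal after the confirming visit.

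Results:

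- About 3% to 6% reach the rule by 48 weeks. 0.03 × 60 = 1.8 and 0.06 × 60 = 3.6, so about 2 to 4 participants.
- About 40% of these are confirmed only at the last treatment visit, so they lose follow-up data but no treatment-period eGFR.
- Their mean true slope is about −5 to −8 per year, against roughly −3 to −3.7 in the rest.
- Widening the assumptions (slope SD 2 to 6, residual SD 3 to 5) gives 3% to 8%, about 2 to 5 of 60. Five cases would give 46/60 = 76.7%.

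**4. Effect on the slope.** Each withdrawn participant's missing visits were filled along that participant's own fitted line, which is one reading of linear trend at point.

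- Example (slope SD 3, 30% rule): the control mean moves from −3.87 to −4.15, the TQF mean from −3.13 to −3.38, and the difference from 0.75 to 0.77.
- Over the settings, each arm's mean decline becomes about 0.15 to 0.29 per year steeper. Against 3.79 that is 0.15/3.79 = 4% to 0.29/3.79 = 8%. The cause is that withdrawal follows two low readings, and the fitted line extends their measurement error forward.
- The difference between arms shifts by about 0.01 to 0.02, and by no more than 0.03 in any setting. With LOCF the shift is no more than about 0.01. For a mixed model on observed data, with variances taken as known, it is under 0.005.

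Withdrawal for prohibited herbs or non-adherence was not simulated; the documents give no rate for either.

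**5. The analysis set.** Table 1 puts randomization at week 2 and the first post-baseline assessment at week 14. A participant who leaves in those 12 weeks without an assessment is outside the full analysis population. One who is withdrawn later stays in it, with later values imputed.

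**The case against.** The strongest case against is that little is lost. Withdrawal triggered by observed eGFR is largely missing at random for a mixed model, and the sensitivity analysis without imputation would be of that kind. A reader might infer that the rule materially biases the treatment comparison; step 4 does not support that for endpoint withdrawals. A reader might also picture the affected participants as the fastest decliners. Under the assumed uniform baseline, about two thirds or more of them started below 25 and qualified largely because they began near 15. Slopes fitted to their readings look steeper than their true slopes because they were selected on noisy values.

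Other points that stand:

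- That visits stop is inferred from the wording about leaving the study. No sentence says so, and a condensed article may leave such procedures to the full protocol. Section 2.12 allows some dropouts to be interviewed, so contact need not end.
- The full analysis population is defined openly and is a common modified-ITT set. Withdrawn participants with one post-baseline value remain in it, so the set definition itself is not contradicted.
- An endpoint case still counts as an event in the time-to-event analysis.
- Greater herb use in the placebo arm may be suspected, but participants are blinded with a matched placebo and no figure supports a difference.
- Removal for not following instructions is discretionary.
- The reason for withdrawal goes on the CRF, so endpoint cases can be separated afterwards, and the article states no retention threshold that they could cross.

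What does not answer the point: recording a reason does not change the printed retention definition, and no analysis restores values never collected. The article does state a withdrawal rule, and that rule does not separate treatment from follow-up.

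**Conclusion.** The point holds as a defect of a stated rule with limited numerical effect. Sections 2.8.3 and 2.11 withdraw participants because of the outcome under study or of behaviour after randomization, and nothing printed keeps them under observation. This does not fit the ITT principle in section 2.14 and distorts the retention measure in section 2.9.1.

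Size: about 2 to 4 of 60 participants, 1.7 retention points each, and a shift of about 0.01 to 0.02 mL/min/1.73m² per year in the slope difference (at most 0.03). The larger effect is on each arm's mean decline, 0.15 to 0.29 per year steeper under linear-trend imputation. That matters for a pilot whose estimates are to feed a full-scale trial.

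All of this rests on assumed thresholds, variances and baseline distribution, and on reading withdrawal from the study as the end of visits. The effect of herb-related withdrawal is unknown. The documents do not support a claim of material bias between arms or of different herb use by arm. The point merits correction, with moderate confidence, but is not critical to the trial's validity.

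**What to change.** Reconcile sections 2.8.3, 2.9.1, 2.11 and 2.14:

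- Define stopping study treatment and leaving the study as separate statuses. Only withdrawn consent, death or loss to follow-up ends data collection.
- Keep the scheduled 12-weekly visits to week 62 for participants who reach an eGFR-based endpoint, use prohibited herbs or do not adhere.
- Analyse them as randomized. Record dates of dialysis or transplant and leave later eGFR values out of the slope.
- Report endpoint events separately from attrition in the retention and completion rates.
- Call the full analysis population modified ITT.

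Rules on stopping study treatment are left as they are.

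Cost: protocol wording, one CRF field, and visits already in the schedule for a few participants. The trial is described as ongoing and missed visits cannot be recovered, so the change should be made soon.

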### Semi-structured interviews

2.12

Individual, semi-structured, in-depth interviews will be carried out with volunteer participants at the end of the trial. The nested semi-structured interview aims to address the following research questions: 1) what expectations, motivations, experiences, and compliance do participants associate with their involvement in the trial, and how do these factors influence their engagement? 2) what are the main challenges and barriers participants encountered while taking the TQF granules and adhering to the trial procedures, and how did they navigate them? 3) what are the feasibility and acceptability of trial procedures (including recruitment, intervention protocol, outcome assessments, and data collection methods) with participants?

The target population is participants from two groups of the pilot trial at Guangdong Provincial Hospital of Chinese Medicine. Eligible criteria: 1) participants who have completed the treatment and follow-up or dropped out but completed at least 12 weeks of treatment and one post-treatment assessment; 2) be able to read and speak Chinese (Mandarin); 3) agree to provide informed consent (including the radio recording). The participants will be selected by purposeful and convenience sampling strategies. The purposeful sampling is to select the participant who can provide the maximum amount of information regarding age, gender, disease stages, medical history, and the trial’s preliminary results. Convenience sampling means choosing the most straightforward examples to save participants and researchers money, time, and effort. It is anticipated that 16 to 24 participants from the trial will be recruited for the qualitative interview (40). Data saturation will be obtained when no new information is discovered in the additional interviews. A separate consent will be provided before the commencement of the qualitative interview.

Interviews will be conducted in a separate room of study sites. Each interview will take about 30-60 minutes. Interviews are semi-structured and guided by an interview guide. A pilot interview will be conducted before the formal interview to test the interview guide. The interview will be conducted in Chinese (Mandarin or Cantonese) and recorded by audio/video. The non-verbal communication, such as facial expressions and body movements, will be taken down by another trained researcher. The interviewer can change the order of questions and details in the interview guide according to the specific situation in the interview with flexibility. Participants are encouraged to speak freely about their experiences and compliance in taking part in the trial. The topic of interest will cover the experiences and expectations of TQF intervention, randomization, recruitment, informed consent process, issues with treatment compliance, and appropriateness of data collection forms/questionnaires and outcome measurements.

### Data collection and management

2.13

Data will be collected from CRF and related files by the researchers via the data entry software EpiData version 3.1. The data will be double-entered by two researchers and checked by another researcher. De-identified data will be entered into a secure computer database that will be used for this study only.

Data storage and security align with China’s Centre for Drug Evaluation guidelines (38). During the study, the blood, urine, and feces specimens from participants will be collected and stored according to the standard operating procedures for 10 years after the completion of the study, and the samples will be destroyed when the storage life ends. CRF collected in this study will be stored securely for 15 years after the completion of the study. Data will be stored in locked cabinets, and all electronic files will be stored in a password-protected, non-networked computer in a locked room at GPHCM. Access will only be by authorized personnel involved in the research. Data will not be stored on laptop computers or removed from the clinical trial site.

### Statistical analysis

2.14

The quantitative data will be processed and analyzed by an independent statistician at GPHCM using PASW 18.0 (IBM SPSS Inc., Armonk, New York, USA) and Stata (Version 15.0, Stata Corp. College Station, TX, USA) with two-tailed 5% significance.

We will perform the primary analysis on the full analysis population following the Intent-to-Treat (ITT) principle. The full analysis population refers to randomized participants who received at least one dose of treatment and had baseline data along with at least one post-baseline efficacy assessment. We will also conduct a per-protocol analysis as a secondary analysis, including participants who completed the study without significant protocol violations. Safety analysis will be performed on the randomized participants who have received at least one dose of TQF or placebo.

Descriptive analysis will be performed on demographic and baseline characteristics. Categorical variables will be summarized as frequencies and percentages. The difference between the two groups will be assessed with a *chi*-squared test. Continuous variables will be reported as means with standard deviations for or medians with interquartile ranges. The difference between the two groups will be detected by Student’s *t*-test for normally distributed data, or the Mann-Whitney U-test for non-normally distributed variables.

The primary efficacy outcome eGFR slope will be assessed through a linear mixed-effects model in which treatment and the interaction of treatment and time are treated as a fixed effect while the time effect is a random effect using an unstructured covariance matrix. A secondary analysis for the eGFR slope will be conducted through the superiority test with a 95% confidence interval (CI), to explore any clinical disparities associated with TQF.

The secondary outcome time to composite renal endpoint events will be analyzed by the Kaplan-Meier method. The log-rank test will be employed to compare time to composite outcomes between the two groups, followed by Cox proportional hazards regression to estimate hazard ratios with 95% CIs. Other continuous outcomes will be performed by Student’s *t*-test or Mann-Whitney U-test, while categorical variables will be examined using the *chi*-square test or Mann-Whitney U-test. The Cochran-Mantel-Haenszel test will be used for categorical variables, adjusting for center-related effects. Subgroup analysis will consider risk factors including but not limited to age, gender, hypertension, and proteinuria. Additionally, the Fisher exact test will be utilized to compare the incidence rates of adverse events and adverse drug reactions throughout the treatment duration.

An ITT analysis will be applied using the imputation method for missing data. We expect less than 20% of missing data points. The linear trend at point method will be used to replace missing values. The existing series will be regressed on an index variable scaled from 1 to n, and the missing values will be replaced with their predicted values. If the predicted values cannot be computed, the last observation carried forward (LOCF) method will be used. We will perform a sensitivity analysis without imputation to assess the robustness of our results.

The semi-structured interviews will be transcribed verbatim. NVivo 11 software will be used to manage and code the data. Grounded theory will be used as a theoretical framework guiding the analysis of interview data, providing a systematic and rigorous approach to understanding complex phenomena within the clinical trial context (41). We will identify and conceptualize relevant themes on the participants’ experiences and expectations of TQF intervention and trial process. A content analysis will be used to analyze the interviews following six phases developed by Kuckartz (42). Firstly, we will get familiar with the original transcripts through repeated reading. Secondly, we establish an initial thematic framework from the keywords or recurring words mentioned by the interviewees in the transcripts. Thirdly, codes will be created for all information after establishing the initial theme framework in NVivo. Further, the content will be coded correspondingly through constant comparison. Next, themes will be defined and interpreted. Finally, we will complete reporting and documenting.

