**Methods:**

A mixed methods research design will be used in this study. A randomized, double-blind, placebo-controlled pilot trial will evaluate the feasibility, efficacy, and safety of TQF compared to placebo on kidney function for people with stage 2-4 DKD. An embedded semi-structured interview will explore the acceptability of TQF granules and trial procedures from the participant’s perspective. Sixty eligible participants with stage 2-4 DKD will be randomly allocated to the treatment group (TQF plus usual care) or the control group (TQF placebo plus usual care) at a 1:1 ratio for 48-week treatment and 12-week follow-up. Participants will be assessed every 12 weeks. The feasibility will be assessed as the primary outcome. The changes in the estimated glomerular filtration rate, urinary protein/albumin, renal function, glycemic and lipid markers, renal composite endpoint events, and dampness syndrome of Chinese medicine will be assessed as the efficacy outcomes. Safety outcomes such as liver function, serum potassium, and adverse events will also be evaluated. The data and safety monitoring board will be responsible for the participants’ benefits, the data’s credibility, and the results’ validity. The intent-to-treat and per-protocol analysis will be performed as the primary statistical strategy.

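### The per-protocol set requires study completion while reaching a renal endpoint counts as withdrawal, so the set is selected on outcome; the abstract and section 2.14 also disagree on its rank

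*Protocol article*

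**What the plan says.** Three parts of the protocol article bear on this.

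- **Analysis sets (2.14).** The main analysis is on the full analysis population: "We will perform the primary analysis on the full analysis population following the Intent-to-Treat (ITT) principle". That set needs one dose, baseline data and one post-baseline efficacy assessment; it does not need completion. Then: "We will also conduct a per-protocol analysis as a secondary analysis", "including participants who completed the study without significant protocol violations". Completion of the study is not defined there.
- **Withdrawal (2.11).** "Participants will be considered withdrawn if they state an intention to withdraw, reach composite renal endpoint events, or become lost to follow-up". The following sentence shows that this means leaving the study and not only stopping treatment: "the researcher must determine the primary reason for premature withdrawal from the study".
- **The composite (2.9.2 and 2.14).** Its components are "receipt of a kidney transplant, initiation of maintenance dialysis, death from kidney failure, a sustained low eGFR, and a sustained percent decline in eGFR". On the analysis: "The secondary outcome time to composite renal endpoint events will be analyzed by the Kaplan-Meier method", with a log-rank test and Cox regression. No analysis set is named for it.

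On the rank of the per-protocol analysis, the abstract differs from 2.14: "The intent-to-treat and per-protocol analysis will be performed as the primary statistical strategy".

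**The concern.** A per-protocol set should be selected on what participants did: took the study medication and kept to the protocol. Here a participant can take every sachet, attend every visit, reach dialysis or a sustained eGFR decline, and be left out because of that event. The selection is on the outcome.

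Two results are exposed. For the time-to-composite outcome, the excluded participants are the ones with events. For the eGFR slope, the primary efficacy outcome, two of the five components (sustained low eGFR and sustained percent decline) are computed from the same eGFR series as the slope, so the fastest decliners are the ones removed. Entry is allowed down to an eGFR of 15 (2.4.1), so some participants start close to any low-eGFR threshold. The Discussion says the pilot is to help estimate the effect size for a full-scale trial, so a flattering slope in each arm could be carried forward.

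**Working it through.** **1. The plan's own figure.** Section 2.5 asks for 25 per arm with about 15% attrition: 25 / 0.85 = 29.4, rounded up to 30 per arm, 60 in total. This matches the stated 60, which is used below.

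**2. The two rules side by side.** Endpoint reached → withdrawn (2.11) → premature withdrawal from the study (2.11) → study not completed → outside the per-protocol set (2.14). Nothing in the article exempts endpoint participants or counts an endpoint as completion.

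**3. Composite events.** The article gives no event rate, so a risk p over the study of 3% to 20% is assumed.

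- Full analysis population: expected events = 60p, from 60 × 0.03 = 1.8 to 60 × 0.20 = 12. Chance of at least one = 1 − (1 − p)^60, from 84% to more than 99.9%.
- Per-protocol set, literal reading: 0 events at every p. The log-rank test and hazard ratio cannot be computed.
- Per-protocol set, lenient reading: Table 1 has five post-baseline visits (weeks 14, 26, 38, 50, 62). If events are spread evenly and only those first seen at week 62 are kept, one fifth remain. With risks of 5% in both arms: 30 × 0.05 + 30 × 0.05 = 3.0 events, and 3.0 / 5 = 0.6. With 20% and 10%: 30 × 0.20 + 30 × 0.10 = 9.0 events, and 9.0 / 5 = 1.8. Keeping week-50 events as well would double these to 1.2 and 3.6, still too few for a useful hazard ratio.

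**4. eGFR slope.** From the article: control mean decline 3.79 and difference 0.75 (2.5), and baseline eGFR 15 to 90 (2.4.1). Assumed, because the article does not give them: the decline is per year; slopes are normal with SD 4, 6 or 8; baseline is uniform; the endpoint is eGFR below 15 or a 40% decline by 60 weeks from randomisation. A participant with baseline b and slope s stays in the set if s ≥ max(15 − b, −0.4b) / (60/52). With 400,000 simulated per arm:

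| Slope SD | Excluded, control / TQF | Control slope in set | TQF slope in set | Difference in set |
|---|---|---|---|---|
| 4 | 6.9% / 5.9% | −3.52 | −2.80 | 0.72 |
| 6 | 9.0% / 7.8% | −3.15 | −2.46 | 0.69 |
| 8 | 11.3% / 10.2% | −2.59 | −1.91 | 0.67 |

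The simulated difference before exclusion was 0.745, 0.761 and 0.767 in the three rows, so the last figure carries some simulation error. Replacing the simulation by numerical integration (the truncated-normal mean, averaged over b) gives 0.72, 0.69 and 0.65.

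A second simulation added visit error (SD 3), required two consecutive visits below eGFR 15 or a 30–40% decline, and used slope SDs of 3.75 and 6. Over the same baseline range it excluded 5–10% of controls, moved the control slope to between −3.63 and −3.12, and gave differences of 0.70–0.74.

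**5. Scale.** With 25 per arm, the standard error of the difference from between-person spread alone is SD × √(2/25): 1.06 at SD 3.75 and 2.26 at SD 8. The loss is 0.05 / 1.06 = 5% of a standard error at most in the second simulation, and (0.75 − 0.65) / 2.26 = 4% at SD 8 in the first. The shift in the control arm's own slope is larger: 3.79 − 3.63 = 0.16 up to 3.79 − 2.59 = 1.20, against an MCID of 0.75.

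**The case against.** The best case for the plan has five parts.

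- **The per-protocol renal results are not empty.** A reader might infer that they are. Only the time-to-composite outcome loses its events; eGFR slope, UACR, UPCR and creatinine stay analysable. The article does not say that the composite will be analysed per protocol either. This stands: the zero-event result is conditional on that analysis being run. However, 2.14 introduces the per-protocol analysis without limiting it to certain outcomes.
- **Not every endpoint participant need be excluded.** Completion of the study is undefined, and 2.9.1 ties the completion rate to the treatment phase. On that reading, an endpoint first reached during the 12-week follow-up leaves its participant in the set. This also stands, but endpoints earlier in treatment are still removed, so the selection on outcome remains.
- **Membership rules belong in the SAP.** Fine detail does. Here, though, the article states two rules that give a wrong result when followed; the problem is not a missing detail.
- **The bias is small.** For the slope contrast it is about 5% of a standard error or less, toward no difference, in an analysis that 2.14 calls secondary, in a pilot whose primary outcome is feasibility. This stands. It does not cover the shift in each arm's own slope.
- **Agreement of the two analyses need not be read as robustness.** The only robustness check the article names is the analysis without imputation (2.14). That readers would take per-protocol agreement as support is a plausible inference, not something the article claims.

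**Conclusion.** The concern holds in a limited form. Sections 2.11 and 2.14 together select the per-protocol set on outcome; this follows from the text and needs no assumed figure. Any per-protocol analysis of the composite would have no events on the literal reading, and about 0.6 to 1.8 on average if only last-visit events are kept, under the assumed risks. The per-protocol eGFR slope is estimable but too favourable in each arm. Its between-arm difference falls from 0.75 to about 0.67–0.74 in simulation (0.65 at the lowest once simulation error is removed). Those slope figures rest on assumed endpoint thresholds, slope SDs, baseline distribution and a yearly time unit.

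A reader might go further and conclude that the trial's main efficacy result is compromised. The article does not support that: the full analysis population does not require completion, so this exclusion does not touch it.

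The conflict over rank is separate and plain. The abstract puts per-protocol alongside intention-to-treat as primary; 2.14 makes it secondary. The abstract may be only a loose summary, but the two should agree.

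**What to change.** In 2.14, define the per-protocol set by adherence and absence of significant protocol violations up to the end of treatment or the first composite renal endpoint, whichever comes first. Add that, for per-protocol membership only, reaching a composite endpoint, including death from kidney failure, is not a reason for exclusion.

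Cross-refer to 2.11, so that a participant recorded there as withdrawn for an endpoint is not dropped from the set on that ground. Restricting the sentence to per-protocol membership matters: the completion and retention rates in 2.9.1 are part of the primary feasibility outcome and should be counted as they are now.

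In the abstract, state that the full analysis population (intention-to-treat) is primary and per-protocol secondary, as in 2.14.

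The cost is one or two sentences in 2.14 with the cross-reference and one in the abstract. No new data are needed, and neither the withdrawal rule nor participant management changes.
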